### **6.0 OUTCOME ANALYSIS**

### **6.1 Definition of Primary Outcome Measure (Reference: Protocol p. 20)**

We will assess the magnitude and direction of the effects of hypothesized predictors on substance use. Specifically, we will examine the association between each factor and past year substance use, past 90 days use and number of drinks measured by TLFB. Multivariate logistic/linear regression, adjusting for demographic characteristics, will be performed.

To evaluate the effect of intervention on substance use at 6- and 12-month follow-up, we will perform multivariate logistic regression adjusting for demographics, predictors of substance use and baseline knowledge. Separate models will be used to evaluate effects at 6- and 12-month. Adjusted odds ratios will be computed for comparison between intervention and control groups.

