## 748 **H. Data Analysis Plan**

749 All analyses will be conducted under the principle of intention to treat; all participants will be analyzed  
750 as members of the groups to which they were originally randomized to. To assess baseline  
751 equivalence between intervention group and control group, we will compare distribution of  
752 demographic characteristics using  $\chi^2$  test or Fisher exact test for categorical variables and t-test or  
753 Wilcoxon sign rank test for continuous variables. We will also evaluate equivalence among those lost  
754 to follow-up versus those retained by comparing demographics and outcomes among those lost and  
755 those with complete follow-up.

756 Our primary outcome variables will be initiation and escalation of substance use. Initiation of use will  
757 be defined as any new use of substances at follow-up among those reporting no past-12-month use at  
758 baseline. For alcohol use, escalation will be defined as, among drinkers, any increase in number of  
759 drinks (measured by TLFB) from baseline to follow-up. For marijuana use, escalation will be defined  
760 as, among users, any increase in days of smoking marijuana (measured by TLFB) from baseline to  
761 follow-up.

762 We will assess the magnitude and direction of the effects of hypothesized predictors on substance  
763 use. Specifically, we will examine the association between each factor and past year substance use,  
764 past 90 days use and number of drinks measured by TLFB. Multivariate logistic/linear regression,  
765 adjusting for demographic characteristics, will be performed.

766 To evaluate the effect of intervention on substance use at 6- and 12-month follow-up, we will perform  
767 multivariate logistic regression adjusting for demographics, predictors of substance use and baseline  
768 knowledge. Separate models will be used to evaluate effects at 6- and 12-month. Adjusted odds ratios  
769 will be computed for comparison between intervention and control groups.

770 We will also evaluate how well the change of intermediary measures predicts the change of  
771 substances use. We will use multiple logistic regression incorporating all intermediary variables.  
772 Separate models will be used to assess the associations at 6- and 12-month.

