## 2.0 SUMMARY OF STUDY DESIGN AND PROCEDURES

### 2.1 Study Objectives

#### 2.1.1 Primary Objectives (Reference: Protocol: p.1, p.8, p.9)

The primary goal of this project is to develop a tailored screening, brief intervention and referral to treatment (SBIRT) model for youth with chronic medical conditions (YCMC) for delivery at point of care during a routine healthcare visit, through conducting a rigorous randomized control trial among adolescent patients with type-1 diabetes (T1D) or rheumatologic conditions.

Building onto an earlier phase of this project (Validating Adolescent SBIRT Measures), we will assess the validity and acceptability of a subset of brief substance-specific questions that are strongly associated with reports of current substance use behaviors and harms and that predict future substance use behaviors and harms.

Screening, tailored feedback and psychoeducation will all be delivered electronically. The brief intervention will target perceived risk of harm of a given substance, knowledge about substances, knowledge of disease specific and medication interactions, and intentions to use. These intermediary measures may serve as proxy markers that can be tracked and may predict substance use trajectories during a long term follow up period.

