### **2.2 Study Design and Procedures**

#### **2.2.1 Study Design (Reference: Protocol p. 6)**

The proposed project is a randomized control trial to assess the efficacy of an SBIRT model tailored to youth with chronic medical conditions. This trial is being built into a larger, longitudinal cohort study to assess whether a set of brief, substance specific questions can accurately predict adolescent substance use outcomes when compared to more lengthy, criterion standard assessment questions, in cross-sectional and prospective analysis.

The first component of the project will consist of pre-testing an assessment battery and brief electronic intervention with a small sample of 14-17 year old youth. In the second component we will randomize consented eligible participants into intervention or control arms of the study and administer the 1) Baseline Assessment Battery and the 2) Brief Intervention OR Brief Control Information. In the third component we will follow up with all participants at 6 and then 12 months after study entry to reassess rates of substance use through the follow up assessment batteries.

At baseline, we will also attempt to enroll parents of all participants who are present at the time of enrollment. We will separately consent and administer a brief assessment battery to parents to assess their knowledge and attitudes of YCMC substance use, as well as opinions and attitudes regarding other health and risk behaviors.

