### **6.4 Analyses of the Secondary Outcome Measures (Reference: Protocol p. 21)**

We will also evaluate how well the change of intermediary measures predicts the change of substances use. We will use multiple logistic regression incorporating all intermediary variables. Separate models will be used to assess the associations at 6- and 12-month.

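### The 6- and 12-month prediction models name no term for randomised arm, although the intervention targets several of the predictors

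*Supplement*

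**What the plan says.** Prediction is part of the SAP's primary objective. Section 2.1.1 states: "we will assess the validity and acceptability of a subset of brief substance-specific questions", and these are to be questions that predict later behaviour and harm. Section 2.2.1 says the cohort in which the trial sits is meant to "assess whether a set of brief, substance specific questions can accurately predict adolescent substance use outcomes", both cross-sectionally and prospectively. Section 6.3 plans to compare answers on likelihood of future use with use reported later in follow-up.

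The intervention acts on the same ground. Section 2.1.1: "The brief intervention will target perceived risk of harm of a given substance, knowledge about substances", along with knowledge of interactions and intentions to use. It calls these measures possible proxy markers for later use. Under section 2.2.4 the baseline battery comes before the intervention.

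The models are as follows.
- SAP 6.1, first paragraph: "we will examine the association between each factor and past year substance use, past 90 days use and number of drinks measured by TLFB". The covariates are given by "Multivariate logistic/linear regression, adjusting for demographic characteristics, will be performed". No time point is given. Protocol section H has the same plan, opening with "We will assess the magnitude and direction of the effects of hypothesized predictors on substance".
- SAP 6.3 and 6.4, on change in intermediary measures against change in use: "We will use multiple logistic regression incorporating all intermediary variables", in separate models at 6 and 12 months.
- SAP 6.1, second paragraph: a treatment-effect model at 6 and 12 months that compares arms and also adjusts for predictors and baseline knowledge.

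The dated updates in SAP section 11 cover stratified randomisation, the alcohol outcome, the mixed model for the treatment effect and a post-hoc subgroup question. They do not touch the predictor or change models.

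**The concern.** Youth in one arm receive, straight after the baseline measurement, material meant to change several of the candidate predictors and the outcome. A follow-up model that ignores arm then averages over treated and untreated youth. Three quantities could be affected: the risk attached to a given baseline answer, the odds ratio of a baseline predictor, and the link between change in an intermediary measure and change in use. The last is the most exposed, because arm can move both sides of the association. What is at stake is whether the prediction results describe the measures themselves or partly reflect the randomised treatment. This matters for a project that wants risk thresholds and proxy markers specific to these youth (Protocol section A; SAP 2.1.1).

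**Working it through.** **Inputs.** SAP 9.0 gives the planning odds ratio (2.0, control versus intervention), intervention-arm prevalence .20 to .55, 300 completers and power .80. SAP 8.0 gives p < .05; two-sided is assumed. No allocation ratio is stated; 1:1 is assumed.

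**The plan's own figure.** With 150 per arm, a two-sided test of two proportions and odds ratio 2.0, power is .745 at prevalence .20, .795 at .25, .825 at .30, .847 at .40 and .820 at .55. The stated .80 is therefore met from about .25 upward, but not at .20. Nothing below depends on this; only the odds ratio and the prevalence range are carried forward.

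**Step 1: absolute risk.** With intervention risk p, control odds = OR × p/(1 − p), control risk q = odds/(1 + odds), pooled risk = (p + q)/2 and gap = q − pooled. For p = .20 and OR 2.0: odds = 2 × .25 = .50, q = .50/1.50 = .333, pooled = .267, gap = .067.

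| p | q at OR 2.0 | pooled | gap | gap at OR 1.5 | gap at OR 1.25 |
|---|---|---|---|---|---|
| .20 | .333 | .267 | .067 | .036 | .019 |
| .30 | .462 | .381 | .081 | .046 | .024 |
| .40 | .571 | .486 | .086 | .050 | .027 |
| .55 | .710 | .630 | .080 | .049 | .027 |

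At OR 1.0 the gap is zero.

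**Step 2: odds ratio of a baseline predictor.** Take a binary predictor with control-arm odds ratio 3.0 and control risk .20, .30 or .40 when the predictor is absent. Average the two arms within each predictor level, then form the odds ratio. For .30 with the intervention halving the odds in everyone: predictor absent, (.300 + .176)/2 = .238; predictor present, (.563 + .391)/2 = .477; odds ratio = (.477/.523)/(.238/.762) = 2.9.

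| Intervention effect on the odds | Pooled odds ratio (true 3.0 in controls) |
|---|---|
| Halved in everyone | 2.91 to 2.93 |
| Halved only in those with the risk factor | 2.10 to 2.16 |
| × 0.4 with the risk factor, × 0.8 without | 2.09 to 2.19 |
| Halved only in those without it | 4.07 to 4.15 |

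**Step 3: change models.** This is a simulation of 400,000 subjects. Change in the intermediary = d × arm + standard normal noise. The log-odds of use start from a risk of .40 and fall by log 2 in the intervention arm and by b per SD of change.

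| d (SD) | True OR per SD | Without arm | With arm |
|---|---|---|---|
| 0.2 | 1.00 | 0.97 | 1.00 |
| 0.5 | 1.00 | 0.92 | 1.00 |
| 0.8 | 1.00 | 0.89 | 1.00 |
| 0.2 | 0.74 | 0.72 | 0.74 |
| 0.5 | 0.74 | 0.69 | 0.74 |
| 0.8 | 0.74 | 0.66 | 0.74 |

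Here leaving out arm overstates the association. The set-up lets arm affect use by routes other than the measure in the model. If the whole effect ran through that measure, this distortion would vanish.

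**The case against.** The other side has real strength.

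- The first paragraph of 6.1 gives no time point. Its outcomes look back and are also collected at baseline, before any intervention, so a baseline analysis is a natural reading, and arm cannot affect one. This stands. It limits the point about 6.1 to any use of that model at follow-up. It does not reach 6.3 and 6.4, which are explicitly at 6 and 12 months.
- Pooling is inferred from silence. This also stands: the documents never say the arms are combined, only that no arm term is listed.
- The second paragraph of 6.1 already holds a prospective model with arm and predictors. True, and it can supply arm-adjusted coefficients for baseline predictors. But it is specified for the treatment effect, has no interaction and does not cover change in intermediaries.
- A baseline answer cannot be altered by what follows it. Correct. Only its relation to later use can differ by arm.
- Nothing in the documents names prediction in untreated youth as the target. Controls are not wholly untouched either: serious use is reported to clinicians, with no restriction by arm stated.

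A reader might infer that pooling must understate natural-course risk, by 11% to 20%, and that a more effective intervention must make the questions look worse. The documents do not support this. Those percentages are the Step 1 gaps relative to control risk (.067/.333 and .080/.710) and concern absolute risk, which 6.1 does not estimate. They also rest on 1:1 allocation and on odds ratio 2.0, the smallest effect in the power statement and not a forecast; Protocol section B expects small individual effects. For odds ratios the bias is near nil under a uniform effect and of either sign otherwise.

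**Conclusion.** The point holds in limited form. The prediction and change models name no arm term, the intervention targets several of the measures in them, and no update repairs this. The consequence depends on the model. Absolute risk, if reported, would lie 6.7 to 8.6 points below control-arm risk at odds ratio 2.0, 1.9 to 2.7 points below at 1.25, and level with it if the intervention has no effect. A baseline predictor's odds ratio is nearly safe under a uniform effect, but can be wrong in either direction if the effect differs by predictor level. The sponsor's own post-hoc question in section 11 supposes that the effect differs by baseline alcohol risk. The change models in 6.3 and 6.4 carry the clearest risk, a spurious association of about 0.97 to 0.89 per SD for arm shifts of 0.2 to 0.8 SD. The figures rest on 1:1 allocation, the illustrative effect sizes shown and, in the change models, an effect of arm on use outside the measured change. Baseline cross-sectional analyses, including any concurrent check of the brief items against the calendar measure, are unaffected.

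**What to change.** Amend the SAP as follows.
1. In 6.1, first paragraph, state the time point or points at which the predictor model is fitted. Leave baseline cross-sectional models as they are.
2. Include randomised arm in every 6- and 12-month predictor and intermediary-change model under 6.1, 6.3 and 6.4.
3. Name a short list of key predictors and add an arm-by-predictor term for each. The main effect of arm removes confounding by arm; only the interaction shows whether the association differs between arms.
4. Report the arm-specific associations beside the overall arm-adjusted estimate. Making the control arm the only validation result is a debatable trade-off and is not needed.

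This takes SAP wording and a few more model terms on data already planned. The price is precision: with 1:1 allocation, an arm-specific estimate rests on about 150 of the 300 completers, so its standard error is roughly √(300/150) = 1.4 times that of the overall estimate. Confining the interactions to key predictors keeps the number of extra terms small.

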#### Changes to the protocol:

- To revise measurement battery assessment for baseline and 6 and 12 months follow up
- Inclusion of post intervention survey and new educational intervention materials
- Addition of a new cohort (inflammatory bowel disease patients in the gastroenterology clinic), and to increase the eligibility age bracket to include patients who are 18 years old at baseline.
- Revision of sample size for enrollment to 300 subjects at BCH, 450 overall
- Addition to allow participation at other study sites.
- Revision to the protocol smart form, protocol, and assent forms to account for changes noted above.

In relation to the above changes, inclusion criteria have been modified as the following:

We recruit patients from the Endocrinology, Rheumatology, and Gastroenterology Clinics at Boston Children's Hospital.

Eligibility Criteria: Inclusion for Patient:

- (Endocrinology Clinic) – Diagnosis of type 1 diabetes for at least one year
- (Rheumatology Clinic) – Diagnosis of a rheumatic condition (appropriate for intervention materials) for at least one year
- (Gastroenterology Clinic) – Diagnosis of Inflammatory Bowel Disease (Crohn's or Colitis) for at least one year
- Adolescents 14-18 years of age.
- Ability to read and understand English at a middle school level or greater.
- Consent to 6 month and 12 month follow up assessments.

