### **2.2.5 Measures (Reference: Protocol p. 9-18)**

**Health information:** Past medical history may inform a participant's decisions to use or abstain from alcohol and other drug use. Youth may use illicit substances to self-medicate, or may avoid substances because of specific health concerns. We will ask participants to report past medical history, and to rate their overall health. We will use previously validated questions to assess these domains. A question on past medical history about being treated with prescribed medications for anxiety, depression, or ADHD was created novel for this battery.

**Other factors that may affect substance use:** Multiple components of the day to day life of youth may predict a relationship to substance use patterns. Predictors of interest for this project include social support, parental monitoring and communication, sleep, and family medical history.

**Current mental health status:** The PHQ-2 is a self-administered, 2-item scale for detecting depression using DSM-IV diagnostic criteria. The PHQ-2 has been studied extensively in large populations and

comes with considerable evidence for its validity. The PHQ-2 has been used extensively in primary care settings and adolescent populations. We will be administering the full PHQ-2 at baseline, 6 month follow up, and 12 month follow up.

The GAD-2 is a self-administered, 2 item scale to screen for anxiety disorders. It has high sensitivity and specificity for detecting generalized anxiety disorder and has been used in primary care settings. We will be administering the full GAD-2 at baseline, 6 month follow up, and 12 month follow up.

**Alcohol, tobacco, marijuana, and use of other substances:** We will administer a series of questions about frequency of substance use and validate them against the criterion standard TLFB.

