### **6.2 Analysis of the Primary Outcome Measure (Reference: Protocol p. 20)**

All analyses will be conducted under the principle of intention to treat; all participants will be analyzed as members of the groups to which they were originally randomized to. We will examine the impact of the psychoeducation program on alcohol use, measured from baseline to twelve months, taking into account correlations within individuals, using multivariate mixed-effects models.

Our primary outcome variables will be initiation and escalation of substance use. Initiation of use will be defined as any new use of substances at follow-up among those reporting no past-12-month use at baseline. For alcohol use, escalation will be defined as, among drinkers, any increase in number of drinks (measured by TLFB) from baseline to follow-up. For marijuana use, escalation will be defined as, among users, any increase in days of smoking marijuana (measured by TLFB) from baseline to follow-up.

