## **11.0 UPDATES TO STATISTICAL ANALYSIS**

### **Updates in relation to 6.0 OUTCOME ANALYSIS**

Updated Date: 11/15/2016

The randomization checklist includes stratification by age and gender at each site. Within each stratum, treatment assignments will be randomly generated and assigned.

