#### **Defining Outcomes**

Primary Outcome(s): Past 3-month alcohol use measured by a Brief Frequency variable for alcohol use.

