#### **Data Analysis Approach**

The impact of the psychoeducation program on alcohol use, measured from baseline to twelve months, taking into account correlations within individuals, using multivariate mixed-effects models adjusting for baseline characteristics.

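### No effect model names site, a randomisation stratum, and the plan does not say how baseline drinking enters: it is absent from the 6.1 logistic covariates and unconstrained in the mixed model

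*Supplement*

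**What the plan says.** **Logistic models.** SAP 6.1 (also SAP 2.1.1 and Protocol Section H) fits separate models at 6 and 12 months by "multivariate logistic regression adjusting for demographics, predictors of substance use and baseline knowledge". SAP 2.2.5 explains the predictors: "Predictors of interest for this project include social support, parental monitoring and communication, sleep, and family medical history". Baseline alcohol or marijuana use is not among them.

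**Mixed model.** SAP 6.2 analyses alcohol use "measured from baseline to twelve months, taking into account correlations within individuals, using multivariate mixed-effects models". The 12/16/2020 update in SAP 11.0 repeats this, "using multivariate mixed-effects models adjusting for baseline characteristics", without listing the characteristics. The 6/27/2019 update makes the primary outcome "Past 3-month alcohol use measured by a Brief Frequency variable for alcohol use". Neither update withdraws the 6.1 models.

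**Randomisation.** The 11/15/2016 update in SAP 11.0 states: "The randomization checklist includes stratification by age and gender at each site". The May 2017 amendment includes "Addition to allow participation at other study sites" and "Revision of sample size for enrollment to 300 subjects at BCH, 450 overall", so about one third of participants may come from outside the main hospital.

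**Data held.** The brief frequency items, the 90-day Timeline Follow Back (TLFB) calendar for those reporting alcohol use, and lifetime use among past-year non-users are all in the baseline battery.

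**The concern.** Earlier drinking is likely to be among the best predictors of later drinking, and it is measured before allocation. A plan that does not say how it enters the effect model can give away efficiency at no benefit. It also leaves the analyst to choose the parameterisation later. Similarly, a factor that allocation was balanced on belongs in the model; otherwise the model-based standard error ignores the balance achieved. At stake are efficiency and pre-specification. The validity of the randomised comparison is not in question.

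**Working it through.** **1. The plan's own power figure.** SAP 9.0 claims 0.80 with 300 completers, odds ratio (OR) 2.0 and p<.05, for intervention-arm prevalence .20 to .55. I assume 150 per arm and a two-sided test, since neither is stated. The control rate q solves q/(1−q) = 2p/(1−p).

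| p | q | power |
|---|---|---|
| .20 | .333 | 0.745 |
| .25 | .400 | 0.795 |
| .30 | .462 | 0.825 |
| .40 | .571 | 0.848 |
| .55 | .710 | 0.820 |

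The claim is essentially met from .25 upward and missed at .20; one-sided, it is met throughout. That shortfall is a separate matter. Here it shows only that there is little spare power at the low end.

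**2. What each model names.**

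| Factor | 6.1 logistic | 6.2 mixed | 12/16/2020 update |
|---|---|---|---|
| Age, gender | within demographics | not listed | probably, but unlisted |
| Site | no | no | not named; set unlisted |
| Baseline use | no | as a repeated response | as a repeated response; covariate not stated |

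**3. Mixed model.** Take a linear outcome with variance σ², baseline-to-follow-up correlation ρ, n per arm and complete data.

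- Unconstrained arm-by-time contrast (difference in mean change): variance (2/n)·2σ²(1−ρ).
- Arms constrained to a common baseline mean, or baseline as a covariate: variance (2/n)·σ²(1−ρ²), ignoring a small-sample term.
- Ratio: (1−ρ²)/[2(1−ρ)] = (1+ρ)/2.

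The documents give no ρ. At assumed values of 0.4, 0.5 and 0.6 the ratio is 0.70, 0.75 and 0.80, so the standard error is multiplied by √0.70 = 0.84, √0.75 = 0.87 and √0.80 = 0.89. Against a follow-up-only comparison, with variance (2/n)σ², the unconstrained contrast has relative variance 2(1−ρ) = 1.2, 1.0 and 0.8. At ρ = 0.4 it is therefore less efficient than ignoring baseline. The SAP does not say which contrast is tested.

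**4. Logistic models.** Simulation: 300 participants, two sites 2:1, equal allocation within site, 30.8% baseline users (past-year alcohol use in the prior study, Protocol Section C), about 30% event rate at average covariates without intervention effect, 1,500 trials per setting. Site and baseline-use ORs are assumptions. The outcome is binary in the whole sample, and the comparison model has arm only.

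| Site OR | Baseline-use OR | Model | Rejection, no effect | Power, OR 2 | Mean SE, OR 2 |
|---|---|---|---|---|---|
| 2 | 1 | arm | 0.047 | 0.812 | 0.242 |
| 2 | 1 | arm + site | 0.050 | 0.814 | 0.247 |
| 4 | 1 | arm | 0.036 | 0.758 | 0.241 |
| 4 | 1 | arm + site | 0.045 | 0.789 | 0.257 |
| 2 | 4 | arm | 0.049 | 0.730 | 0.241 |
| 2 | 4 | arm + site + baseline | 0.054 | 0.775 | 0.259 |
| 2 | 12 | arm | 0.053 | 0.558 | 0.239 |
| 2 | 12 | arm + site + baseline | 0.051 | 0.667 | 0.288 |

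Simulation error on a rejection rate near .05 is √(.05×.95/1500) = 0.006, so only the site OR of 4 shows a visible conservative shift. Adding baseline use raises the standard error of the log odds ratio and raises power as well, because the conditional effect is larger.

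**5. Initiation and escalation.** Initiation is confined to participants with no past-year use, so past-year use is constant there; lifetime use is the only further use history named above. Escalation is any increase over the participant's own count. A participant with a zero 90-day count can only stay or rise, while one with a high count tends to fall back. The starting count is therefore prognostic for the endpoint, and defining the endpoint against it does not adjust for it.

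**The case against.** The strongest reply is that the latest primary analysis is the mixed model, which already uses baseline, and that the quoted covariate list belongs to text the later updates have overtaken. Much of this stands. A reader might infer that the primary analysis ignores baseline drinking and so loses the full 1−ρ². The documents do not support that: SAP 6.2 and the 12/16/2020 update run from baseline with within-person correlation. A reader might also infer that chance baseline imbalance goes uncorrected, but a change contrast subtracts it.

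A second inference, that the standard errors are misleading because the strata are ignored, is also too strong. Age and gender fall under demographics in 6.1, leaving site. Site could lie within the unlisted baseline characteristics, and leaving it out errs on the conservative side.

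Two things remain. Having baseline as a response is not the same as constraining or conditioning on it, and the plan states neither. The 6.1 models are not withdrawn, and their covariate list omits baseline use. It is fair to say that both parameterisations of the mixed model are valid; the choice between them is one of efficiency and should be made in advance.

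**Conclusion.** The point holds as a gap in specification with a real but conditional cost in efficiency.

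- **Mixed model:** if fitted as an unconstrained arm-by-time model, a common baseline mean would cut the variance of the contrast by 20 to 30%. This assumes a linear outcome, complete data and ρ between 0.4 and 0.6. The outcome is a frequency variable, so the gain under a count or binary model will differ.
- **Logistic models:** if 6.1 still applies, omitting baseline use costs power, illustrated as 0.73 against 0.78 at an assumed baseline-use OR of 4, and 0.56 against 0.67 at 12. This applies to use in the whole sample. It does not carry over to initiation, and the gain shrinks if the other predictors already carry part of the same information.
- **Site:** negligible at a site OR of 2 and modest at 4 (power 0.76 against 0.79). The documents give no site effect.

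Nothing here suggests a biased test or inflated type I error.

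**What to change.** In SAP 6.2 and 11.0:

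1. Include site, age stratum and gender as fixed effects in the primary mixed model. Define site: the stratification note is dated before the amendment that opened other sites, so the word could mean clinic or centre. State how small sites are grouped.
2. Constrain the arms to a common baseline mean, or model the follow-up responses with baseline past-3-month frequency as a covariate. Name the contrast and visit tested.
3. List the remaining baseline characteristics.
4. Say whether the 6.1 logistic models still apply. If so, add the baseline TLFB count (drinks, or marijuana days) to the escalation models and, optionally, lifetime use to the initiation models.

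This changes SAP wording only and needs no new data. If outcome data have already been examined, date the change and report the specified model beside the one already fitted.
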